## Abstract

**Introduction:** Personal lifestyle and air pollution are potential risk factors for major non-communicable diseases (NCDs). However, these risk factors have experienced dramatic changes in the Beijing–Tianjin–Hebei (BTH) region in recent years, and few cohorts have focused on identifying risk factors for major NCDs in this specific region. The current study is a large, prospective, long-term, population-based cohort study that investigated environmental and genetic determinants of NCDs in BTH areas. The results of this study may provide scientific support for efforts to develop health recommendations for personalized prevention.

**Methods:** About 36,000 participants 18 years or older would be obtained by multistage, stratified cluster sampling from five cities for the baseline assessment. Participants underwent seven examinations primarily targeting respiratory and circulatory system function and filled out questionnaires regarding lifestyle behavior, pollutant exposure, medical and family history, medication history, and psychological factors. Biochemistry indicators and inflammation markers were tested, and a biobank was established. Participants will be followed up every 2 years. Genetic determinants of NCDs will be demonstrated by using multiomics, and risk prediction models will be constructed using machine learning methods based on a multitude of environmental exposure, examination data, biomarkers, and psychosocial and behavioral assessments. Significant spatial and temporal differentiation is well-suited to demonstrating the health determinants of NCDs in the BTH region, which may facilitate public health strategies with respect to disease prevention and survivorship-related aspects.

## Introduction

It is well-known that large cohort studies play essential roles in gaining knowledge about diseases and reducing their associated burden (1). Stroke, ischemic heart disease, and traffic injury are the top three leading causes of years of life lost (YLLs) in China (2). The risk factors contributing to the loss of disability-adjusted life-years include inappropriate dietary habits such as high sodium consumption (15.9%), hypertension (13.3%), tobacco use (12.5%), and air pollution (9.3%) (3). The area around the capital of China, called the Beijing–Tianjin–Hebei (BTH) region, is the political, economic, and cultural center of China. In the BTH area, ischemic heart disease is the leading cause of YLLs, and inappropriate dietary habits result in high sodium consumption. In 2016, the “Healthy China 2030 Plan” was launched by the State Council. According to this plan, health-related risk factors for non-communicable diseases (NCDs) will be under effective control by 2030, including an increase in the proportion of individuals taking physical exercise and a reduction in the per-capita daily salt intake by 20% (4). As residents in the BTH area may experience a significant change in lifestyle risk factors in the next few decades, a cohort study is necessary to explore the effect of health determinant changes on NCDs and to demonstrate the effect of changes due to health-related strategies.

Air pollution is an important trigger of myocardial infarction (MI), and the population attributable fraction of fine particle matter is ~5% (5). Recent systematic reviews and meta-analyses have demonstrated the harmful effect of short-term ambient particle matter and gaseous pollutants [NO_2_, carbon monoxide (CO), CO_2_] on MI (6), stroke (7), and arrhythmia (8), but the evidence is less consistent for ozone (O_3_). Several studies in Western countries have evaluated the adverse health effects of long-term PM_2.5_ exposure and have demonstrated that long-term exposure to even low PM_2.5_ concentrations (PM_2.5_ ranging from 6.3 to 13 μg/m^3^) could promote cardiovascular events and increase cardiovascular mortality (9–11). In China, long-term exposure to air pollution has been shown to be associated with a higher prevalence of cardiometabolic risk factors, especially hyperbetalipoproteinemia (12). Another study from China demonstrated that long-term exposure to PM_2.5_ was independently associated with incident hypertension at relatively high ambient concentrations (13). Although various studies have demonstrated the adverse health effects of ambient air pollutants, some of them did not take potential indoor air pollution into consideration, which may lead to overestimation of the effect size. A study in Beijing showed a dose–response relationship between short-term PM_2.5_ exposure (PM_2.5_ ranged from 3.9 to 494 μg/m^3^) and ischemic heart disease (IHD) morbidity and mortality that was supralinear (14). However, evidence on the dose–response relationship between long-term exposure to air pollution and health effects is still limited. The full dose–response curve needs to be better elucidated because of its huge impact on global public health. In the current cohort study, regions with different concentrations of air pollution exposure were selected as survey sites, which can provide evidence about the dose–response relationship between long-term pollution exposure and NCDs.

Fine particulate matter (PM_2.5_) exposure contributes to high mortality in Beijing (15). The overall concentration of pollutants from northwest to southeast is gradually increased in the BTH region. In the BTH region, some cities, such as Baoding and Shijiazhuang, have extremely high concentrations of PM_2.5_ (16), whereas some cities, such as Chengde, have good natural environments and air quality. This geographical distribution of pollutants will generate natural exposure groups, which can be used to explore the role of pollutants in NCD pathology. To address heavy pollution in China, the Air Pollution Prevention and Control Action Plan was issued in 2013 by the State Council of China. With the implementation of the Action Plan, the emissions of sulfur dioxide (SO_2_), nitrogen oxide (NO_X_), and PM_2.5_ decreased by >30% in 2017 compared with the emissions in 2012 in the BTH region (17, 18). Thus, the severity of air pollution varies not only among regions but also over time. Because of the significant spatial and temporal differentiation of pollutant distribution, studying a cohort in the BTH region will play an essential role in demonstrating the effect of pollutants on the etiology of chronic disease.

Cohorts based on natural communities will improve the understanding of a wide range of risk factors for NCDs. The prospective China Kadoorie Biobank (CKB) is the largest cohort in China. Previous studies have demonstrated many lifestyle, environmental, and genetic risk factors for chronic diseases in the Chinese population (19–22). However, the determinants of disease consist of genetic, epigenetic, environmental, and lifestyle risk factors that interact with one another and operate within the larger physical-sociocultural environment. Thus, it is unrealistic to find a common effective solution for disease prevention. The BTH region is not included in the CKB cohort. However, as the BTH region has a unique socioeconomic status (SES) and political function, it is important to find health determinants of NCDs in this specific region.

In recent years, many policies have been introduced and implemented in the BTH region that affect lifestyle, SES, and air pollution. In 2017, the Xiong'an New Area was established in Hebei Province to evacuate some industries from Beijing, such as the high-energy consumption industries and enterprises with less innovation and technology. The Xiong'an New Area mainly includes three counties in Hebei Province, which previously were mostly agricultural areas (23). The municipal government of Beijing, some tertiary hospitals, universities, large wholesale markets, and factories are moving from the urban area of Beijing to its suburbs to reduce traffic congestion and the severity of air pollution. These strategic changes in the BTH region will have a tremendous impact on the SES of residents and will gradually improve the air quality. Therefore, establishing a community-based cohort in the BTH region will be especially effective in exploring the impact of SES and air pollution on common chronic diseases.

## Methods and Analysis

### Objectives

To monitor the epidemic trends of major NCDs.To demonstrate the etiology and pathogenesis of major chronic diseases with consideration of environmental, lifestyle behavior, genetic, and psychological factors.To screen biomarkers of air pollution–related cardiopulmonary diseases and construct disease risk prediction models.

### Outcomes of Interest

Number of deaths and cause of death.Incident of major NCDs, such as hypertension (*ICD-10*: I10-I15), diabetes (*ICD-10*: E10-E14), ischemic heart disease (*ICD-10*: I20-I25), cerebrovascular disease (*ICD-10*: I60-I69), chronic obstructive pulmonary disease (*ICD-10*: J44), and cancer (*ICD-10*: C00-C97).Intermediate phenotypes or key risk factors for NCDs, including anthropometric factors and physiological, lifestyle, and environmental factors.

### Study Design and Settings

The CoHort study on CHronic disease of Community Natural population in Beijing–Tianjin–Hebei region (CHCN-BTH) is a population-based prospective cohort study, which has been registered with the Chinese Clinical Trial Registry (ChiCTR1900024725).

The sample size was estimated using the Cox regression module in PASS-NCSS 11.0 software. The parameters are as follows: statistical power is 80%, significance level is 0.05, and the lowest event rate is 50 per 100,000 (cardiovascular morbidity is ~650 per 100,000, and mortality is ~250 per 100,000; lung cancer morbidity is ~70 per 100,000, and mortality is 50 per 100,000). The log hazard ratio (HR) of PM_2.5_ per 10 μg/m^3^ is ~0.25 (HR = 1.28), the standard deviation of PM_2.5_ (per 10 μg/m^3^) is 1.4, and the *R*^2^ of PM_2.5_ with other covariates was set to 0.2. The lowest sample size was 32,037 according to the calculation of PASS software. Thus, the cohort was designed to recruit 36,000 individuals living in Beijing, Tianjin, and Hebei provinces by expecting a 10% loss to follow-up. The survey sites are shown in Figure 1. The CTCH-BTH cohort will include 30,000 community-lived individuals and 6,000 participants who undergo routine physical examinations. Most of the participants in the baseline survey were of the Chinese Han population, and ~10% of the participants were of Manchu ethnicity.

**Figure 1 F1:**
[figure not shown]
Sampling set of CHCN-BTH.

### Sampling Methods

The cohort study was established with a multistage, stratified cluster sampling method. The cities are first selected according to geographical region, SES, and medical service quality. In the first stage, three cities were chosen as survey sites located in the southern, central, and northern parts of Hebei Province. Beijing and Tianjin are also designated survey sites. Among the above survey sites, the severity of air pollution and economic status are significantly different from each other, which can reflect the state of the natural population in Hebei Province. In the second stage, we selected districts from urban cities and counties from rural areas. In the next stage, communities were selected from districts in urban areas, while townships were selected from counties in rural areas. The new district called Xiong'an, which previously contained three rural counties, has now integrated into one urban city. In the final stage, residents in the selected area will be invited to participate in the study considering the demographic structure of the sixth national census. These procedures can ensure the representation of the sampling. Finally, the selected survey sites included 41 communities, 36 townships, and 7 functional units in five cities. Details of the sampling are shown in Figure 2.

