China is a multiethnic country. There are 55 minorities in China in addition to the Chinese Han population. Most of the cohorts in China only contain the Han population. We will recruit not only a Chinese Han population in the cohort but also a Manchu population of ~10%. Manchu is one of the most populous minorities in the BTH region. Based on the sixth China national population census, Manchu was the largest minority group in Hebei (3.02%) (35). The Manchu population prefers sticky foods and a high-salt diet, and their prevalence of several diseases, such as hypertension and diabetes, is different from the Han population (36). Studies focusing on both Manchu and Han populations may help us to find more specific determinants of chronic disease in the BTH region. Moreover, the genetic background of the Manchu population is also different from that of the Han population (37). Given that population stratification will lead to spurious results and poor reproducibility in genetic association findings, grouping individuals into ethnic clusters will be effective in controlling population heterogeneity.

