There are several limitations of the current cohort. First, the survey sites and the participants will not be randomly chosen. This is because the current study focuses on selected survey sites with various economic, medical, and environmental characteristics to better demonstrate the pathogenic mechanism of NCDs. In the central functional district of Beijing, we selected Chaoyang district. Tianjin and Shijiazhuang are in good terms of social economics with moderate air pollution, while Baoding is a city with moderate economic status and severe air pollution. Chengde city was selected as having better air quality. Xiong'an city may experience rapid economic development in the next 5 years. The residents' socioeconomic level and lifestyle may undergo tremendous changes, which may have a certain impact on health. Moreover, instead of estimating the prevalence of diseases by representative sampling, this cohort study is more concerned about the proportion of participants who could be followed up. Thus, we chose stable communities and participants to ensure a good follow-up rate. During the study recruitment process, the investigator will explain that enrollment in the cohort requires continued follow-up. Subjects who actively choose to join the cohort may have a stronger willingness to participate compared with randomly chosen participants, which may avoid loss to follow-up. Second, the current cohort will exclude participants with major physical and mental disabilities and any who could not complete the survey even with the help of investigators. These exclusion criteria may lead to a “healthy cohort” effect, and the results of this cohort study will be more applicable to a healthier population and should be explained and extrapolated with caution. Third, most of the surveys will be conducted on workdays, and elderly people and retirees may prefer to participate compared with young people and employees, which may introduce selection bias. To reduce selection bias and better represent the target population, we will recruit participants considering their demographic structure according to the results of the sixth national census. Finally, the same examination equipment will be used for physical examination to ensure the comparability of measurements. Because of the limited quantity of equipment, it is not possible to carry out repeated measurements at the same time. Therefore, in this study, only 20% of the subjects were repeated measured in each time of follow-up. It was planned to complete repeated measurements of all the subjects after five rounds of follow-up. In order to overcome the shortage of partial repeated measurements, telephone interviews and medical records update will be conducted to all participants every 2 years to obtain the change of lifestyle behavior and other health determinants.

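### Sampling Methods claims a representative sample that the Discussion disclaims, so Objective 1 can be met only as trends within the cohort

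*Protocol article*

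**What the plan says.** The Objectives section lists three aims. The first is "To monitor the epidemic trends of major NCDs", with no target population named and no limit on what the trends refer to.

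Sampling Methods describes the design in these terms: "The cohort study was established with a multistage, stratified cluster sampling method". Cities are picked by geography, socioeconomic status and medical service quality, then districts and counties, then communities and townships. At the last stage, "residents in the selected area will be invited to participate in the study considering the demographic structure of the sixth national census". Two claims about the population follow. Of the contrast between sites in pollution and economy, the section says "which can reflect the state of the natural population in Hebei Province". Of the whole procedure it says "These procedures can ensure the representation of the sampling".

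The limitations part of the Discussion says something else. It states that "the survey sites and the participants will not be randomly chosen", explains that the share of people who can be followed mattered more than representative estimation of prevalence, and concludes: "Thus, we chose stable communities and participants to ensure a good follow-up rate". It adds that people who actively join may be more willing than a random sample. It also names a healthy-cohort effect from the exclusion criteria, and a tilt towards elderly and retired people because most surveys take place on workdays.

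**The concern.** The two sections cannot both stand. A reader who wants to know what the sample represents will go to Sampling Methods, and there finds that representation is assured. The correction appears only in the Discussion and does not refer back to the sentence it overturns.

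This matters for one objective in particular. Associations between exposure and outcome do not strictly need a representative sample. The level of disease in a population, and how that level moves over time, does need one, or else a credible weighting back to the population. With Objective 1 unqualified and the Methods claiming representation, a rate or trend observed in this cohort could be taken as that of Hebei or of the whole region. At stake is which population any reported level or trend may be attached to.

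**Working it through.** The article gives no figure that settles this, so the check is a comparison of its statements.

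**1. Does the described selection produce representation?** Sampling Methods names a multistage, stratified cluster design but describes no stage as random. Cities are chosen on stated characteristics, and residents of selected areas are invited. On its own that might be condensation of a fuller protocol. The Discussion removes the doubt by saying that neither sites nor participants are chosen at random.

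**2. Does the contrast between sites support the Hebei statement?** The basis offered is that the sites differ markedly in pollution and economic status. Spread across sites is what an exposure–response analysis needs. It does not show that the people recruited at those sites resemble the provincial population.

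**3. Does the census provision repair it?** Set the routes of selection that the Discussion names against what recruitment to census structure can balance:

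| Route of selection named in the Discussion | Balanced by recruiting to census structure? |
|---|---|
| Age and employment tilt from workday surveys | Partly: only the demographic variables actually used |
| Stability of communities and participants | No |
| Willingness to join and stay | No |
| Better health through the exclusions | No |

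Three of the four routes are left untouched. Each may plausibly be related to chronic disease, so demographic balance alone does not turn cohort levels into population levels.

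**4. What can Objective 1 still deliver?** The article provides two-yearly follow-up (Table 1 and Follow-Up), committee ascertainment of incident events (Measurements), death surveillance with certificates (Follow-Up), and description of outcomes at baseline and at each follow-up (Statistical Plan). That is enough to describe trends among the people enrolled. The missing link is from those people to the region.

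**5. Is the cohort one group for this purpose?** Study Design and Settings gives 30,000 community residents and 6,000 people from routine physical examinations:

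6,000 / 36,000 = 16.7%.

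Under Follow-Up, the employee-examination group repeats the full baseline examination every 2 years. In the community group at least 20% are remeasured per round, with telephone interviews and medical records otherwise. The two groups differ in how they entered and in how intensively disease is looked for, so a pooled trend would mix two kinds of ascertainment.

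**The case against.** The strongest reply is that the authors have already conceded the point. Non-random selection is the first limitation they list, with reasons, and they ask for caution in extrapolating. Objective 1 names no region and no prevalence, and the use foreseen in the Conclusion concerns determinants of disease, not regional rates. The planned sample size is built on a hazard ratio for PM2.5, to which this point is irrelevant.

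Most of that stands. Nothing is concealed, and the design choice itself is defensible for a cohort that puts retention first. But disclosure in one section does not correct a contrary statement in another, and an objective that names no population is open to being read with the one that the Methods claim to represent.

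Three stronger readings are tempting, and the article does not support them:

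- **That Objective 1 has no support in the design.** The follow-up, event ascertainment and death surveillance described above do support trends within the cohort.
- **That an ageing cohort will show a spurious rise of a given size.** This would require that crude incidence be reported as a trend, and the article specifies no such analysis. The replacement of lost participants, matched by age and sex, does not by itself stop the cohort ageing, but how age is handled may be settled in an analysis plan not shown here.
- **That the Manchu share proves distortion.** About 10% of participants against 3.02% of Hebei gives 10 / 3.02 = 3.3. But the Discussion presents the 10% as intended, and the denominator covers Hebei alone while the cohort also spans Beijing and Tianjin. No regional share is given.

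Nor does it follow that census weighting must be added. Weights on demographic variables would leave selection on stability, willingness and health uncorrected, and weighting may belong in the analysis plan.

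**Conclusion.** The point holds as an internal contradiction with a bounded consequence. Sampling Methods attributes to the sample a property that the Discussion says was neither achieved nor sought. Objective 1 is therefore attainable as a description of trends in this cohort, and not as prevalence or incidence trends of the Hebei or Beijing–Tianjin–Hebei population.

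The reach is two statements in Sampling Methods and one of three objectives. No numerical bias can be derived from the article, and none is claimed. The conclusion takes the Discussion's account of selection as the accurate one, which is reasonable because it is the more specific of the two and gives its reasons. It also assumes that the full protocol contains no selection probabilities that would support inference to the population, which the statement on non-random choice makes unlikely. The objectives on causes, biomarkers and risk prediction are not called into question here.

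**What to change.** 1. In Sampling Methods, delete or qualify both the sentence on representation and the clause on Hebei's natural population. Say instead that sites were chosen purposively for contrast in environment and economy, that participants are volunteers from stable communities, and that census structure guided the demographic mix.
2. Reword Objective 1 along these lines: to describe age- and sex-standardised trends in major non-communicable diseases within the cohort, by city and calendar period. Standardisation is included to make clear what the objective refers to. Its absence from the article is not a complaint.
3. Show community recruits and employee-examination recruits separately whenever a level or trend is reported.
4. State that no prevalence or trend claim will be made for Hebei or the wider region.

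The cost is a few sentences and one split in the descriptive tables, plus a narrower claim for Objective 1. Recruitment, measurement, sample size and the exposure–outcome analyses need no change.
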